#### Recruitment and randomization

2.3.2

Recruitment occurs out on a rolling basis, and screening procedures involve verbal screening of potential participants over the phone. Initially, the screener provides an overview of the Break4Brain Project and then obtains verbal consent. The telephone script includes questions regarding participants’ demographic information such as age, gender, and any history of ADHD, along with inquiries about inclusion and exclusion criteria. The total time administered in all screening questions is approximately 10 min. Recruitment began in January 2024 and is still ongoing. Once parents agree to participate via telephone, they sign a written informed consent before their children participate. In addition to obtaining informed consent from parents or legal guardians, this study will also seek verbal assent from the participating children. Prior to their involvement, children will be provided with age-appropriate explanations about the study’s purpose, procedures, and their role within it. They will be encouraged to ask questions and express any concerns they might have. Only those who verbally agree to participate, after understanding the study, will be included.

Randomization of participants into experimental conditions is conducted using R software by an external statistician. This randomization takes place after baseline assessments to minimize the risk of bias during measurements.

#### Experimental protocol and conditions

2.3.3

Each participant will visit the laboratory for 4 days over 3 weeks (Figure 1). This phase comprises three experimental conditions in a counterbalanced order (Supplementary Figure S1): (i) PA with cognitive engagement, (ii) PA without cognitive engagement, and (iii) cognitively engaging control. Participants will arrive at the laboratory unaware of the experimental condition they will be practicing each day. To minimize the impact of fatigue or excessive physical exertion on performance during the experimental conditions, participants will be advised to avoid intense PA on the day prior to each visit.

##### PA with cognitive engagement condition

2.3.3.1

This experimental condition will involve participants engaging in PA interspersed with rest periods doing cognitive tasks. Following a structured format, it consists of 10 consecutive 30-s blocks of PA alternated with cognitive tasks, totaling 10 min of PA time with a 1:1 work-to-rest ratio. Additionally, there will be 5 min allocated for warm-up and another 5 min for cool-down activities. The PA will target both aerobic and strength-based metabolism, based on the low integration-low relevance movement strategy (Mavilidi et al., 2022).

To determine the PA to be performed, participants will roll a die. Depending on the outcome, they will carry out the corresponding predetermined exercise, which was already introduced during the warm-up session. In the event of a repeat, the evaluator will replace the card for that specific exercise on the die. Conversely, during rest intervals involving cognitive tasks, participants will engage in solving various “tangram” puzzles. The researcher will manage the timing.

##### Physical activity without cognitive engagement condition

2.3.3.2

This experimental condition will involve PA interspersed with rest periods (without doing cognitive tasks). This experimental condition will replicate the dose of the preceding one (i.e., maintaining the same work ratio, and duration). Participants will practice PA guided by video observation and imitation,^2^ based on a protocol that will not require prior experience or knowledge from the participants (Moreau et al., 2017). This video was used by the research staff in a prior study (Gelabert et al., 2023). The PA will also focus on both aerobic and strength-based metabolism, following a strategy with low integration-low relevance movements (Mavilidi et al., 2022).

##### Cognitively engaging control condition

2.3.3.3

Participants will be instructed to watch a video concerning hygiene habits while remaining seated and at rest for 10 min.^3^ The researcher will not interact with the participants during this period. It is important to employ control conditions that closely resemble the intervention being studied. This approach helps isolate the hypothesized mechanism of interest (Simons et al., 2016). In our study, it is more clinically relevant to compare the intervention with behaviors commonly employed in classrooms, rather than solely comparing it against students sitting quietly (Pontifex et al., 2019).

#### Measures

2.3.4

Each participant will individually attend to our laboratory on 4 different days (Figure 1), with a seven-day gap between each measurement day (once at baseline, and three times immediately after each experimental condition). Primary outcomes will be evaluated each day, while the rest will be only assessed at baseline (Table 1A). To mitigate measurement bias, trained researchers will conduct these measurements consistently in the same laboratory setting.

##### Primary outcome measures

2.3.4.1

###### Brain function

2.3.4.1.1

Electroencephalogram (EEG) will be recorded during both the n-back and the flanker tasks. Then, EEG datasets will be processed in Brain Vision Analyzer (Version 2.0.4), as well as through custom code implemented in MATLAB using the EEGLAB toolbox (Delorme and Makeig, 2004). From the EEG, we will obtain Event-related brain potentials (ERPs). ERPs will serve as a measure of brain response to discrete events. Electrophysiological activity will be recorded using 32 active electrodes (i.e., BrainVision actiCAP system, Brain Products GmbH, Munich, Germany). The protocol to acquire ERPs is similar to other studies examining executive functions (Galvez-Pol et al., 2018; Galvez-Pol et al., 2018; Luck, 2014). Next, we will aim to epoch the continuous data to obtain an EEG component known as P3 or P300. This component is characterized by a positive deflection in voltage around 300 milliseconds post-stimulus. It is usually elicited in tasks requiring attention and decision-making, reflecting cognitive processes related to stimulus evaluation and categorization. The P300 amplitude varies with the relevance and probability of the stimulus, serving as a key indicator of attentional and working memory processes (Luck, 2014).

##### Secondary outcome measures

2.3.4.2

###### Academic performance

2.3.4.2.1

The academic fluency index will be calculated, consisting of the reading, mathematics, and writing fluency subtests of the Bateria III Woodcock Muñoz^™^ (Muñoz-Sandoval et al., 2005). Reading fluency will assess the participant’s capacity to read simple sentences rapidly, mathematical fluency will gauge the ability to quickly solve simple addition, subtraction, and multiplication problems, and writing fluency will measure the ability to formulate and write sentences promptly. The median reliability coefficient alphas for all age groups for the standard battery ranged from 0.81 to 0.94.

###### Cognition

2.3.4.2.2

A cognitive test battery covered by working memory, inhibition, and sustained attention will be administered to assess cognitive functions. All the instruments included in the study have undergone prior validation for use with the child population and cover the majority of cognitive domains affected by ADHD disorder (Wade et al., 2020).

####### Working memory

2.3.4.2.2.1

The computerized n-back test will be utilized to evaluate the ability to update information in working memory, a component of executive control (Jacola et al., 2014). Participants will be presented with a sequence of stimuli, in this case fruits, and will need to determine if each stimulus matches the one presented ‘n’ items ago (Supplementary Figure S2). Each of the 336 trials will start with the presentation of a central fixation point, followed by an Inter-Trial Interval (ITI) lasting a maximum of 2,500 ms (varies depending on response time). Stimuli will then promptly appear after the ITI and remain on the screen for 500 ms. The n-back test will be built in Opensesame stimuli presentation software (Mathôt et al., 2012). The median reliability coefficient alpha for this task in children population ranges 0.60–0.80.

####### Inhibition

2.3.4.2.2.2

The computerized flanker test will be used to assess the capacity to inhibit irrelevant stimuli within executive control (Krueger et al., 2009). The test is designed to measure the effect of irrelevant stimuli on cognitive processes. Specifically, participants are tasked with identifying the direction in which a central stimulus (in this case, fishes) is pointing, while simultaneously inhibiting the influence of surrounding distractor stimuli (fishes) (Supplementary Figure S3). Each of the 180 trials will begin with the presentation of a central fixation point, followed by an ITI lasting 1,100 ms, 1,300 ms, or 1,500 ms (variable time). Stimuli will then promptly appear after the ITI and will remain on the screen until the participant responds or up to 3,000 ms. The flanker test will be built in Opensesame stimuli presentation software (Mathôt et al., 2012). The Cronbach’s alpha for the flanker task in children typically falls in the range of 0.70–0.85.

####### Sustained attention

2.3.4.2.2.3

The Conners’ Continuous Performance Test (CPT-3) will be employed to assess sustained attention (McGee et al., 2000). This test will involve presenting a sequence of 360 trials on a screen, displaying letters A through X, with each letter appearing for 250 ms. These trials will be organized into 18 consecutive blocks, each consisting of 20 trials. The intervals between stimuli will vary among the blocks, ranging from 1 to 4 s. The proportion of target stimuli (non-X letters) will remain at 90% of the total trials. The Cronbach’s alpha for the CPT-3 in children falls in the range of 0.70–0.95.

###### Physical activity and sedentarism

2.3.4.2.3

PA and sedentarism will be measured through an objective measure such as accelerometers (Migueles et al., 2017; ActiGraph wGT3x-BT). Participants will be instructed to wear the accelerometer during their participation in the study (21 days). At baseline, a trained researcher will wear the accelerometer on the non-dominant wrist of the participant. Additionally, participants will be given a sheet where they must record when they do not have the accelerometer with them, as well as data related to sleep. They may remove the accelerometer only during water activities, including showering. Programming and data download will be done through the Actilife software (Version 6.13.4, ActiGraph, LLC). Each day that they will come to the laboratory, a trained researcher will charge the battery (once the experimental condition has been done).

###### PA intensity of the experimental conditions

2.3.4.2.4

Intensity of the experimental conditions will be assessed using two instruments:

Heart rate monitor. Participants will wear a Polar H10 (Speer et al., 2020) heart rate (HR) monitor connected to an iPad via the Polar Team application during the experimental conditions. This will allow us to gauge the PA intensity (classified into five resistance zones: 50–59% – 60–69% – 70–79% – 80–89% – 90–100%, of their HRmax).Accelerometer. The same accelerometer worn by participants since the beginning of the study will continue to be used during the execution of the experimental conditions. This device will help measure the intensity of the PA, classifying it as light, moderate, moderate-to-vigorous.

###### Self-report of sedentarism

2.3.4.2.5

Sedentary behaviors will also be evaluated using the Youth Activity Profile—Spain (YAP-S). This self-administered questionnaire consists of 15 items and employs a 5-point Likert scale. It utilizes a 7-day recall format and has been validated for use with children (Segura-Díaz et al., 2021). In our study, participants will only need to respond to the final five questions (items 11–15), which specifically refer to sedentary habits. The Cronbach’s alpha for the YAP-S in children falls in the range of 0.70–0.85.

###### Sleep quality

2.3.4.2.6

Sleep quality will be assessed using the previously introduced accelerometer (ActiGraph wGT3x-BT) with the same data collection procedure as reported before. Moreover, participants will maintain a sleep log, recording details such as wake-up time, daytime sleep episodes, bedtime, sleep onset latency, and any nighttime awakenings.

###### Physical fitness components

2.3.4.2.7

Physical fitness will be evaluated using the ALPHA fitness test battery which determines speed agility by 4×10 shuttle run test, muscular fitness by handgrip strength (with a dynamometer; TKK 5101 Grip D) and standing long jump test (using a non-elastic tape; SECA 201) (Ruiz et al., 2011). Each measurement will be taken twice, and the maximum score of the two measurements will be recorded. Nonetheless, because of space limitations with our equipment, we will be unable to administer the “20-meter shuttle run test” from the ALPHA battery fitness test to assess cardiorespiratory fitness. Instead, we will adopt the validated “3-min step test” protocol (Jankowski et al., 2015). This test will involve using a step with a height of 30.5 cm with a stepping rate set at 96 beats per minute, which will be measured using a metronome. Moreover, the same pulsometer described earlier (Polar H10) will be used to determine the mean HR of one mine after the test (Speer et al., 2020).

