###### Body composition

2.3.4.2.9

For body mass measurement, participants will be instructed to stand barefoot on an electronic scale (TANITA BC 601, Ltd) with an accuracy of 0.05 kg. Height will be measured using a stadiometer (SECA 213 Ltd) with an accuracy of 0.1 cm. Body mass index (BMI) will then be calculated as weight divided by height squared (kg/m^2^). Furthermore, waist circumference will be assessed using a non-elastic tape measure (SECA 201) with a range of 0–150 cm and an accuracy of 0.1 cm. Hip circumference will also be measured using the same non-elastic tape measure. Each measurement will be taken twice, and the mean of the two measurements will be recorded.

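### The rule to record the maximum of two fitness trials, read literally, keeps the slower 4×10 shuttle run while keeping the better handgrip and long-jump trials

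*Protocol article*

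**What the plan says.** Section 2.3.4.2.7 (Physical fitness components, phase I) draws three tests from a fitness battery. It "determines speed agility by 4×10 shuttle run test, muscular fitness by handgrip strength" and adds the "standing long jump test (using a non-elastic tape; SECA 201)". The next sentence sets the recording rule for this group of tests: "Each measurement will be taken twice, and the maximum score of the two measurements will be recorded". No test is excepted.

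The cardiorespiratory test comes after that sentence and has its own measure, a heart rate taken after the test: "Instead, we will adopt the validated “3-min step test” protocol". It is therefore outside the two-trial rule.

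The body composition section (2.3.4.2.9) chooses a different summary: "Each measurement will be taken twice, and the mean of the two measurements will be recorded". So the article sets its summary rules section by section.

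Physical fitness is listed among the phase I secondary outcome measures. On timing, section 2.3.4 says: "Primary outcomes will be evaluated each day, while the rest will be only assessed at baseline". For the fitness tests, Table 1A agrees and marks the 4×10 shuttle run at the baseline visit only.

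**The concern.** A single rule based on the numerical maximum suits several tests only if a higher number means better performance in all of them. That is true of grip force and jump distance. It is not true of a run over a fixed distance scored by time, where the larger number is the slower run. Someone who follows the sentence as written would store each child's best effort on two tests and worst effort on the third, and the three values would not describe the same thing.

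What is at stake is the meaning of the speed-agility variable: as a secondary measure, in describing the sample, and as a covariate if it is ever used as one. There is also a practical point. Section 2.3.2 says that recruitment began in January 2024 and is continuing, and each child does the fitness tests at one visit only. If just the larger value is stored, the better shuttle-run time is lost and no later visit can supply it.

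**Working it through.** **Score direction.** The inputs are the three tests and the rule, all from section 2.3.4.2.7.

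| Test | Quantity | Better performance | Trial kept by the maximum |
|---|---|---|---|
| Handgrip | force (dynamometer) | higher | better |
| Standing long jump | distance (tape) | higher | better |
| 4×10 shuttle run | time over a fixed distance (inferred) | lower | worse |

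The inference in the last row rests on the test being a fixed-distance run that "determines speed agility by 4×10 shuttle run test". The maximum would be right only if the result were turned into a speed or otherwise inverted. The article says nothing of that kind here or elsewhere.

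**Size.** The plan gives no figure to reproduce. Let a child's two times be independent and normal with the same mean and within-child SD σ.

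- The difference D = X1 − X2 is normal with mean 0 and variance 2σ².
- Slower time minus faster time is |D|, with expectation √(2σ²) × √(2/π) = 2σ/√π = 1.128σ.
- By symmetry, the slower trial lies on average 0.564σ above the child's own mean and the faster trial 0.564σ below it.

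The article gives no σ, so a range of 0.2 to 0.5 seconds is assumed:

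- σ = 0.2: 1.128 × 0.2 = 0.23 seconds.
- σ = 0.5: 1.128 × 0.5 = 0.56 seconds.

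This is the average amount by which a literally recorded shuttle-run time would exceed the best-trial time. Handgrip and long-jump values are the same under a maximum rule and a best-trial rule.

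**Reach.** The primary outcome is P3, and fitness does not enter its definition. The conditions are compared within child, and fitness is measured once, before any condition is given. Section 2.3.5 allows adjustment for control variables that prove necessary but does not name fitness. Nor is fitness among the confounding variables in section 2.3.4.3, which cover socioeconomic status, parental education and occupation, and ADHD symptoms.

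**The case against.** The strongest reply is that the sentence is loose rather than wrong. It speaks of a maximum score, not a longest time, and in a fitness section that can mean best performance. The unit of the shuttle run is never stated. Section 2.1 says that the measurement protocols are published separately, and the tests come from a cited battery, so the manual used in the laboratory may already say that the faster run is kept. A journal article commonly leaves trial-level scoring to such a manual.

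Part of this stands. Whether staff actually store the slower run cannot be told from the article, and the point should not be put as though they do. But this is not a detail left out. The article states a specific rule, applies it to a named test, and makes no exception. If practice already differs, the published text misdescribes it and needs the same edit.

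A reader might also infer that the maximum rule biases a comparison of fitness between children with and without ADHD, because keeping the slower run penalises children whose performance varies more. The article does not support this. It specifies no such comparison of fitness, and the models in section 2.3.5 are built on condition and four timepoints, whereas fitness is measured once. The argument is also not specific to the maximum. With within-child SDs σ₁ and σ₂ in the two groups, the slower-trial rule shifts the group difference by 0.564(σ₁ − σ₂), and the faster-trial rule shifts it by the same amount in the opposite direction. With equal SDs both shifts are zero. An effect on a combined fitness score might be inferred too, but no such score is described.

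**Conclusion.** The point holds as a minor one. A stated recording rule points the wrong way for one of the three tests it covers, and nothing else in the article corrects it. Taken literally, it makes the shuttle-run value longer than the best-trial value by about 1.13 within-child SDs on average. The seconds quoted above depend on an assumed SD range and on independent normal trials with a common mean. The conclusion about direction depends only on the run being scored as time.

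The fault is one of inconsistent direction across tests, confined to a baseline secondary measure. It gives no ground for doubting the P3 analysis or the comparisons of the experimental conditions, and it does not show that any child's result has in fact been recorded wrongly.

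**What to change.** Replace the rule in section 2.3.4.2.7 with wording such as: each test is performed twice and the better result is used, namely the highest value for handgrip and standing long jump and the lowest time for the 4×10 shuttle run. State the unit of the shuttle run (seconds) in the same place, and have both trial values stored rather than only the one selected.

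For children already tested, check which shuttle-run value was entered. Where both trials were kept, re-derive the variable as the lower time. Where only one was kept, record whether it was the faster or the slower, so that the two kinds are not mixed without notice.

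The cost is one sentence in the protocol and a short recode. No sample size, visit or primary analysis changes. Because recruitment is open and fitness is measured once, an early correction is nearly free, while a late one may be impossible for children whose second value was not retained.

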###### Motor proficiency

2.3.4.2.8

The short form of the Bruininks-Oseretsky Test of Motor Proficiency (BOT-2) will be used (Bruininks and Bruininks, 2005). The short form is composed of 14 subtests based on fine motor precision, fine motor integration, manual dexterity, bilateral coordination, balance, running speed and agility, upper-limb coordination, and strength. The BOT-2 has been administered in children with ADHD (Adhvaryu et al., 2022). The BOT-2 demonstrates high internal consistency, with Cronbach’s alpha values typically ranging from 0.5 to 0.99 across its various subtests and composite scores.

###### Body composition

2.3.4.2.9

For body mass measurement, participants will be instructed to stand barefoot on an electronic scale (TANITA BC 601, Ltd) with an accuracy of 0.05 kg. Height will be measured using a stadiometer (SECA 213 Ltd) with an accuracy of 0.1 cm. Body mass index (BMI) will then be calculated as weight divided by height squared (kg/m^2^). Furthermore, waist circumference will be assessed using a non-elastic tape measure (SECA 201) with a range of 0–150 cm and an accuracy of 0.1 cm. Hip circumference will also be measured using the same non-elastic tape measure. Each measurement will be taken twice, and the mean of the two measurements will be recorded.

###### Biological maturation

2.3.4.2.10

Using data collected, including gender, age, weight, and height, we will determine the peak height velocity (PHV; Mirwald et al., 2002). To accomplish this, the participant’s brainstem height will be measured using the same stadiometer described earlier. This measurement will be repeated twice, and the average of both will be recorded. Additionally, the length of the lower limbs will be recorded, and calculated by subtracting the brainstem height from the overall height. Furthermore, the velocity of peak height growth (VPM) will be calculated using the equations proposed by Moore et al. (2015).

###### Verbal and non-verbal intelligence

2.3.4.2.11

The Kaufman Brief Intelligence test (K-BIT) will be used to measure verbal and non-verbal intelligence (Cordero and Calonge, 2000). All assessments are grounded in the scores attained from the vocabulary tests, which encompass 45 items of expressive vocabulary and 37 items of definitions, as well as the matrix test consisting of 48 items. This test has been used in children with ADHD (Rodriguez-Martínez et al., 2023). The KBIT- demonstrates high internal consistency, with Cronbach’s alpha values typically ranging from 0.80 to 0.96 across its verbal, non-verbal, and composite scales.

